### Intervention

“The Growth Factory” is an online intervention that aims to empower adolescents with intellectual disabilities. The intervention is based on scientific research on implicit self-theories and mindset interventions by Carol Dweck and David Yeager [16, 36, 39, 51, 52]. A multidisciplinary team of professionals and youth has developed the intervention using a Dutch guideline for effective interventions for people with intellectual disabilities [53]. By using an online approach in the intervention we were able to address the information processing needs of youth with intellectual disabilities. For example, by providing visual and auditory support, using interactive assignments and animations, and the possibility to repeat parts of the session. The adapted intervention has been tested in a pilot study with adolescents with intellectual disabilities and/or psychiatric problems [48]. After that, improvements were made which resulted in the current program “The Growth Factory (2.0)” [54].

“The Growth Factory” consists of six sessions and one booster session, each lasting for 25–40 min. Youth participate in the sessions in a silent room under guidance of a research assistant using a protocol. The assistant will check whether the participant understands the information and provide help if needed. Furthermore, during the sessions the assistant will make observations concerning understanding, pauses needed, attitude, and attention. These and any other important observations will be written down on a checklist after each session.

Before the start of the first session, participants choose an avatar who will guide them through the sessions. Each session has the same structure: (1) previous week’s homework assignments are discussed with the research assistant, (2) a welcome by the avatar including a summary of the previous session and an introduction of the upcoming theme, (3) an animation clip in which the content of the session is explained, (4) two interactive assignments, (5) a summary with the most important messages of the session, (6) a goodbye by the avatar, (7) participants rate their satisfaction with the session, and (8) homework assignments are explained by the research assistant.

In the first session, the participants learn about the plasticity of the brain, that the brain is more like a muscle and that people can grow their brain by ‘exercising’. Specifically, youth are told that the connections in their brain multiply and get stronger when they use them. In session two, participants learn about growth and fixed mindsets. Specifically, they learn that people with a growth mindset believe they can develop their abilities through (mental) exercise. People with a fixed mindset believe people cannot really change and are convinced that abilities, cognitions, and personality are set. In session three, participants learn that a growth mindset helps to accomplish goals. Moreover, they learn that people with a growth mindset will embrace challenges, persist in the face of setbacks, and see effort as a strategy needed to reach one’s potential. Also, participants practise with so called ‘grow thoughts’. In session four, participants learn about the ‘recipe of growth’, which consist of three important ingredients. The first two ingredients of the recipe for growing your brain: ‘effort’ and ‘good strategies’ are taught in the fourth session. To develop abilities and skills, both effort and practise are of great importance. Furthermore, finding the best strategy to accomplish a goal is important. In the fifth session, the third ingredient ‘help from others’ is explained. Participants learn that sometimes it can be rewarding to ask for help or accept help from others. They also learn the five steps to ask for help in an appropriate way. The sixth session is a compilation of the previous sessions. The most important information is repeated. Moreover, this session will be used as the booster session after the 3 months follow-up. In addition, in sessions three, four, and five movie clips are shown about ‘peer role models’ in which these peers share their experiences in how a growth mindset helped them in encountering problems and accomplishing goals. Also, these three sessions contain additional assignments at the end of the session to practise the content of the session with the research assistant. Session three and four contain exercises based on the principles of cognitive behavioral therapy. Youth practise to recognize negative thoughts in a social situation and change these thoughts into so called ‘growth thoughts’. In session five youth practise asking for help using the five steps in a role play.

Every week, the participants receive two messages by mobile phone and/or email containing a reminder of the session’s content or a short assignment. The purpose of these messages is to improve the transfer from the online intervention into daily life. Furthermore, each participant receives a workbook. Every week, a few homework assignments need to be completed. The research assistant discusses homework assignments with the participant before starting the next session.

### Care as usual

Participants assigned to the control condition will receive care as usual. Adolescents recruited from a special education school attend the school curriculum and are supervised by a mentor teacher. In addition, a school psychologist is involved in the educational learning process and provides specific orthopedagogical advise. Each student receives a ‘developmental perspective plan’ based on the youth’s specific developmental needs. Furthermore, additional therapies are offered depending on the youth’s care need, such as resilience training and creative arts therapies (e.g., art, music, and/or dramatherapy). Specifically, for youth with physical disabilities physiotherapy, ergotherapy, and medical assistance are offered. Adolescents recruited from a specialized residential care institute receive an ‘individual treatment plan’ in which treatment goals and plans are formulated based on the youth’s specific developmental needs. A multidisciplinary team is involved in these treatment programs. One of the group care workers is the youth’s mentor who provides guidance and support based on the treatment goals and plans. Furthermore, additional therapies are offered, such as physiotherapy, medication management, and resilience training; and sometimes a family social worker is involved. Also, in residential care youth receive medical assistance when needed. Youth care workers provide care using a “strength based approach” which focusses on the individuals’ strengths, potential, and self-determination.

### Instruments/measures

Instruments will be adjusted to reduce the complexity of the questionnaires for the participants with intellectual disabilities using the Dutch guideline for the development and adjustment of diagnostic instruments for people with intellectual disabilities [55]. The answering categories of the different questionnaires will be unified into one format of answering catergories ranging from ‘completelyuntrue’ to ‘completely true’, and coloured emoticons corresponding with the answering categories will be added. Difficult words and sentences will be simplified or slightly rephrased to avoid misunderstandings due to literal interpretation. The pilot studies showed the questionnaires to be suitable for youth with intellectual disabilities [46]. Table 1 shows an overview of study outcome measures and the informants that will be involved in each assessment.

**Table 1 Tab1:** Overview of assessments

	T0	Session 1–6	T1	T2	T3
Adolescent					
Mindset (MQ)	x		x	x	x
Empowerment (EMPO Youth 2.0)	x		x	x	x
Behavior problems (BPM-Y)	x		x	x	x
Self-esteem (RSES)	x		x	x	x
Treatment motivation (MYTS)	x		x	x	x
Therapeutic alliance (TASC-r)	x		x	x	x
Challenge seeking (Puzzles)	x		x	x	x
Impact of social exclusion (Cyberball game)	x		x	x	x
Intervention satisfaction (SRS)		x			
Mentor^a^					
Mindset (MQ)	x			x	x
Empowerment (EMPO Youth 2.0)	x			x	x
Behavior problems (BPM-P)	x			x	x

^a^Mentor is defined as school mentor or social worker from the group

### Screening measures

For all participants, information regarding gender, age, IQ scores, and diagnosis will be provided by the treatment coordinator or school psychologist. Participants will provide information about setting (residential care group or homestay) and attributional treatment (e.g., physiotherapy, speech therapy, social skills training).

### Primary outcome measure

*Mindset* will be measured with the Mindset Questionnaire (MQ) [46]. The MQ consists of two parts: (1) two subscales measuring youth’s implicit theories: mindset emotion/behavior (6 items, e.g., ‘I can control the feelings I have’) and mindset intelligence (3 items, e.g., ‘I can learn new things, but I can’t really change my basic intelligence’), and (2) the subscale ‘perseverance’ measuring youth’s self-regulatory behavior (9 items, e.g., ‘If something does not work, I quit’ and ‘By practising a lot I’m getting better’). The original 6-point Likert scale was replaced by a 5-point Likert scale [56], ranging from *1* (‘completely untrue’) to *5* (‘completely true’), with higher scores indicating a higher endorsement of a growth mindset. Furthermore, the pilot studies showed that the MQ is suitable for youth with intellectual disabilities [46] and the validity and reliabilities of the subscales ranged from just sufficient to satisfactory [46]. In addition to self-report of youth, participants mentor will complete the MQ about their view on participant’s mindset and self-regulatory behavior.

### Secondary outcome measures

*Empowerment* will be measured with the Dutch questionnaire ‘EMPO Jongeren 2.0’ (EMPO Youth 2.0) [25]. The EMPO Youth 2.0 consists of 16 items measured on a 5-point scale ranging from *1* (‘completely untrue’) to *5* (‘completely true’). The subscale ‘intrapersonal’ contains 9 items (e.g., ‘I am in control of myself’) as the scale ‘interactional’ consists of 7 items (e.g., ‘I make use of advice or support from people around me, if necessary’). The sum of the scores on all items yields a total empowerment score. The EMPO Youth 2.0 demonstrates sufficient reliability [25, 46]. Also adolescent’s mentor will complete the EMPO Youth 2.0 questionnaire about their view on adolescent’s empowerment.

*Internalizing, attention and externalizing behavior problems* will be assessed using the Dutch translation of the ‘Brief Problem Monitor-Youth’ (BPM-Y) [57, 58]. The BPM-Y contains 19 items measuring internalizing problems (6 items), attention problems (6 items), and externalizing problems (7 items). The sum of the scores on all items yields a total problems score. The items will be rated on a 3-point scale. The original categories ‘not true’, ‘somewhat true’, and ‘very true’ were replaced with ‘completely untrue’, ‘not true/ not untrue’, and ‘completely true’ to match with the answering categories in the other questionnaires. An example item of the externalizing problems scale ‘I threat other people’. The BPM-Y demonstrates sufficient and satisfactory reliability [46, 57]. In addition, adolescent’s mentor will complete the questionnaire about their view on behavior problems using the parent version of the BPM, the ‘Brief Problem Monitor-Parent form’ (BPM-P) [57]. This scale offers good to excellent internal consistency and acceptable to good test-retest reliability [57].

*Self-esteem* will be assessed using the Dutch translation of the ‘Rosenberg Self-Esteem Scale’ (RSES) [59]. The scale is a 10-item Likert scale with items answered on a 4-point scale. The original four answering categories ‘strongly agree’ to ‘strongly disagree’ were reformulated into ‘completely untrue’ to ‘completely true’ to match the answering categories in the other questionnaires. An example item is ‘I am able to do things as well as most other people’. The instrument possesses satisfactory reliability [46, 60].

*Treatment Motivation* will be measured with the Motivation for Youth’s Treatment Scale (MYTS) [61], an eight item measure that assesses problem recognition (e.g., ‘My behavior is making my life worse’) and treatment readiness (e.g., ‘If I attend counseling I think my life will get better’). In addition, completion of the MYTS yields a total score for overall motivation. The original 5-point answering categories ‘strongly disagree’ to ‘strongly agree’ were replaced with ‘completely untrue’ to ‘completely true’. Three changes were made in the treatment readiness scale, because participants at the institutional care already receive counseling. Therefore, the word ‘extra’ was added to the sentences about getting counseling (e.g., ‘Getting *extra* counseling seems like a good idea to me’). Furthermore, the sentence ‘Complete these two questions only if you get extra counseling’ was added because not all pupils already receive extra assistance. Moreover, the question ‘I get extra counseling because others think I need it’ was added to complete the questionnaire. The original version of the MYTS offers a brief and reliable tool to assess treatment motivation among youth and caregivers. The internal consistency of this instrument is good [61].

*Therapeutic alliance* will be measured with the Dutch translation of the Therapeutic Alliance Scale for Children, revised (TASC-r) [22]. The instrument contains 12 items covering both postive and negative aspects of therapeutic alliance, and distinguishes between the affective bond (6 items, e.g., ‘I like spending time with my therapist’) and client-therapist collaboration (6 items, e.g., ‘I’d rather do other things than meet with my therapist’). In addition, completion of the TASC-r yields a total score for overall alliance. The word ‘therapist’ is reformulated into ‘mentor’ to better fit the target group. Before participants start to complete the questionnaire the assistant will make clear about whom (mentor from school or youth care group) the questionnaire has to be filled in. The original items are rated on a 4-point Likert scale ‘not true’ to ‘very much true’. These categories were changed into the 5-point answering categories ‘completely untrue’ to ‘completely true’ to match the answering categories of the other measures used. The scale has demonstrated adequate internal consistency and validity in previous investigations [22, 62].

*Challenge seeking* will be assessed by using the experimental task ‘puzzles’, based on the measure ‘challenge-seeking: hypothetical scenario’ [20] and the idea of Koestner’s ‘hidden figure puzzles’ [43] to measure willingness to seek challenges. The task consists of three puzzles, each presented in an envelope. The envelops contain respectively an ‘easy’, ‘medium’, and ‘difficult’ puzzle. Participants will be asked to choose a puzzle and answer the question why that specific puzzle is chosen, but participants do not actually complete the puzzle. The choice of challenge level and the reason why that specific puzzle is chosen will be reported by the research assistant.

*Impact of social exclusion* will be measured by using the ‘Cyberball game’ [63]. In this game, the participant plays two virtual ball-toss games with three others who are presented to be real and connected through a network. The ‘others’ are in fact controlled by the computer program. In the first game the youth plays a ‘normal’ tossing ball game and will receive the ball as often as the other players. In the second game it is tested whether the participant will be affected by victimization. After receiving the ball a few times the participant is excluded by the other players and no longer receives the ball during the game. After completing both games, a post experimental questionnaire [64] will be assessed. The questionnaire contains 11 statements to measure the impact of the exclusion on belonging (‘I feel I belonged to the group’), mood (e.g., ‘How do you feel?’), perception of group cohesiveness (e.g., ‘I do not like the other players’) and intensity of ostracism (e.g., ‘I feel I was being excluded by the other players’). Three questions about meaningful existence, control, and self-esteem of the original 12 items questionnaire were deleted. Two new statements served as a manipulation check (e.g., ‘The other players are real participants’). The original 9-point answering categories were replaced by a 5-point scale with different categories, e.g., ‘completely untrue’ to ‘completely true’, ‘very bad’ to ‘very good’, and ‘very sad’ to ‘very happy’. Furthermore, the desire for vengeance after exclusion is measured by providing participants the opportunity to take revenge by allocating hot sauce to one of the peers by whom they were excluded during the second Cyberball game. Participants will be told that the other player dislikes spicy food, but has to consume the entire amount of hot sauce anyway. The research assistant will report the amount of allocated hot sauce in grams using a digital weighing scale. Finally, the youth will play the first version of the Cyberball game again.

Participants’ safety during data collection for the Cyberball and Hot Sauce paradigms is guaranteed. First, during the experiment the exclusion experience is brief, mild, and quickly followed by an inclusion experience. Second, participants will be debriefed immediately after the experiment, following a standardized protocol. Participants will be told the exclusion happened due to a computer error and the players will not have to eat the hot sauce. Furthermore, studies in other special needs populations also obtained ethical permission for this experiment [65, 66] and have shown participants did not express regret or distress at having taken part in the Cyberball game [64, 65]. After debriefing, the participant will have to answer three more questions about their mood to check if they feel relaxed and unthreatened. The Cyberball task takes approximately 10 min.

#### Intervention satisfaction

Participants in the intervention group will grade their satisfaction after each session of “The Growth Factory” with a score from *1* (very low) to *10* (very high). This grading system is in line with the Dutch educational system. The mean of the grades per session will provide a mean session satisfaction grade. Furthermore, the mean of these satisfaction grade scores of the six sessions will be taken to construct an overall mean intervention satisfaction grade. In addition, intervention satisfaction will be measured with a Dutch translation and adaptation of the Session Rating Scale (SRS) [67]. Participants will complete four statements, e.g., ‘The assistant listened to me today’ (relationship), ‘What we did today is important to me’ (goals and topics), ‘I liked what we did today’ (approach and method) and ‘I hope next time we will do something similar’ (overall). The original 10-cm visual analog scale will be replaced by a 5-point Likert scale ranging from ‘completely untrue’ to ‘completely true’. The average score of the four items will be taken as an indicator of the satisfaction with each session (session SRS). Subsequently, to construct an overall intervention satisfaction score (intervention SRS) the average will be taken of the session satisfaction scores of the six sessions. The scale has demonstrated a satisfactory reliability and validity in previous research [67]. Finally, participants will be asked to answer two open questions as a qualitative measure of session satisfaction: ‘What did you like about today’s session?’ and ‘What did you not like about today’s session?’

### Statistical analyses

Following the intention-to-treat principle, the data from all participants randomized to either the intervention or control group will be analysed. Multiple imputations will be used for missing values at post-intervention and follow-up measurements. In addition, a completers only analysis will be conducted (i.e., participants that completed five or six sessions). The results will be reported in accordance with the CONSORT Statement [49].

Possible baseline differences between the two groups in background variables (e.g., age, gender) and relevant study variables will be examined using independent-sample t-tests. In case of differences at baseline, variables will be included as covariates in all models testing the effectiveness of the intervention. Furthermore, the effectiveness of the intervention will be analysed using repeated measures ANOVA for differences within subjects (i.e., pre-test, post-test, follow-up 1, and follow-up 2 measurements) and between subjects (intervention versus control group). In addition, intervention satisfaction, level of intellectual disability, age, baseline mindset, and gender will be tested as moderators of the effects of the online mindset intervention.

These moderator effects will be tested using three-way interactions in our repeated measures design. The effect of the mindset intervention on the secondary outcomes measures, (i.e., empowerment, internalizing problems, attention problems, externalizing problems, and total behavior problems, self-esteem, treatment motivation, therapeutic alliance, challenge seeking, and impact of social exclusion) might be mediated by mindset. This will be tested in several mediation analyses in Mplus [68].

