The primary aim of the present study therefore is to examine the effectiveness of the online intervention “The Growth Factory” using a full scale randomized controlled trial (RCT) with four measurement moments. “The Growth Factory” aims to empower youth with intellectual disabilities by stimulating the development of a growth mindset and thereby positively impacting their psychosocial development. We hypothesize that adolescents in the intervention group will show larger increases in growth mindset (primary outcome). Furthermore, we hypothesize that adolescents in the intervention group will show greater improvements in empowerment, self-esteem, treatment motivation, and therapeutic alliance as well as a larger reduction of internalizing problems, attention problems, externalizing problems, and total behavior problems compared with adolescents in the control group (secondary outcomes). Finally, we hypothesize that adolescents in the intervention group will seek challenges more and will be less negatively impacted by social exclusion compared with adolescents in the control group (secondary outcomes). In addition, the secondary aim of this study is to gain insight for whom the intervention “The Growth Factory” is effective (i.e., moderation) and how the intervention works (i.e., mediation). Intervention satisfaction, level of intellectual disability (mild intellectual disability versus borderline intellectual functioning), and baseline mindset will be tested as moderators of the effects of the online mindset intervention. We hypothesize that adolescents with higher intervention satisfaction scores, borderline intellectual functioning, and a fixed mindset at baseline will show larger increases in growth mindset compared to adolescents with mild intellectual disabilities, who report less satisfaction with the intervention, and a more growth oriented mindset at baseline. In addition, we will explore whether age and gender moderate the intervention effect. Finally, we will test the mediating role of mindset on the effect of the mindset intervention on the secondary outcomes measures.

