### Participants

Participants that will be selected for the study are (late) adolescents (12 to 23 years) with mild to borderline intellectual disabilities, including youth with mild intellectual disabilities (IQ 50–69) and borderline intellectual functioning (IQ 70–85) and deficits in adaptive functioning. Besides an intellectual disability participants could have accompanying physical disabilities or psychiatric problems. Participants are clients in residential care or students in special education. Exclusion criteria are the presence of severe emotional problems hindering participation in the study, such as extreme aggression problems or an acute unstable mental condition. Participants who agree to participate will be included in the study when both adolescent and parents or legal representative provide written informed consent.

A power analysis [50] was performed to calculate the sample size required in the present study. Based on previous research on the effectiveness of mindset interventions in education [39], the expectation is to find a small to medium effect (*d* = 0.25). The power calculation (two-tailed, alpha 0.05, statistic power 0.80) based on a three measurements design shows that 106 participants are necessary. Therefore, our aim is to include *N* = 120 participants (*n* = 60 intervention group; *n* = 60 control group) in the RCT taking into consideration 10% attrition.

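### Effectiveness is tested by a repeated measures ANOVA with the pre-test as an outcome level; modelling T1-T3 with the T0 score always as covariate, and one named contrast, would use the same data better

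*Protocol article*

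**What the plan says.** Under Statistical analyses, the protocol article states that "the effectiveness of the intervention will be analysed using repeated measures ANOVA for differences within subjects". It lists pre-test, post-test and both follow-ups as the within-subject levels and arm as the between-subject factor. Moderators, baseline mindset among them, are tested as three-way interactions in the same design.

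Background and study variables are compared between arms at baseline by t-test. Those that differ become covariates in every effectiveness model. For gaps in the data, "Multiple imputations will be used for missing values at post-intervention and follow-up measurements".

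The Background predicts a larger increase in growth mindset in the intervention arm as the primary outcome and gives no time point. Under Participants, the effect is d = 0.25, and "The power calculation (two-tailed, alpha 0.05, statistic power 0.80) based on a three measurements design shows that 106 participants are necessary". The target is raised to 120 for 10% attrition. Neither the within-person correlation nor the expected time course is given.

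**The concern.** The hypothesis is simple and directional: mindset rises more with the intervention. The natural group effect in the planned model is a group-by-time interaction on 3 degrees of freedom. It asks whether the two profiles differ in any way, has no direction, and does not by itself give one effect estimate with an interval.

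The pre-test also has two roles:
- As an outcome level, it spends information on an occasion where randomisation makes the expected difference zero. As a covariate, the same score would reduce the error variance at T1-T3.
- When baseline mindset is tested as a moderator, T0 mindset is predictor and outcome at once. The same happens if the t-test rule brings T0 mindset in as a covariate: that outcome level is then explained entirely by the covariate. The rule also makes the final model depend on a significance test.

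At stake are power in a trial sized on a small expected effect, and a clear estimate for the primary outcome.

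**Working it through.** **Inputs from the article.** Two-tailed alpha 0.05, power 0.80, d = 0.25, three measurements, 106 required, 120 randomised 1:1 with 10% attrition (Participants); four occasions T0-T3 (Statistical analyses). Completers: 120 × 0.9 = 108.

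**Assumptions.** Compound symmetry with correlation r, SD 1 at each occasion, and the time course of the effect. The article states none of these, so results are shown over a range.

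**Step 1: reproduce 106.** For the within-between interaction, λ = N·m·f²/(1−r), with f = d/2 = 0.125, m = 3 and r = 0.5. At N = 106, λ = 106 × 3 × 0.015625/0.5 = 9.94 on 2 and 208 df, and power is 80.7%; at N = 104 it is 79.9%. So 106 is reproduced. r = 0.3 would give 146 and r = 0.7 would give 64, so r = 0.5 is inferred.

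**Step 2: formulas for the comparison.** δ is the arm difference in SD units, with δ = 0 at T0.
- Planned interaction: λ = (N/4)·Σ(δ_t − mean δ)²/(1−r) over T0-T3; df 3 and 3(N−2).
- T0-adjusted mean of T1-T3: λ = (N/4)·(mean of δ at T1-T3)²/[(1−r)(1+3r)/3]; df 1 and N−3.
- T0-adjusted T1 difference: λ = (N/4)·δ₁²/(1−r²); df 1 and N−3.
- Joint test of the three T0-adjusted differences: λ = (N/4)·δ′V⁻¹δ, V = (1−r)I + r(1−r)J, where J is a matrix of ones; df 3 and N−5.

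**Step 3: numbers for a sustained 0.25 SD at N = 108 (N/4 = 27), r = 0.5.**
- Planned: 27 × 0.75 × 0.0625/0.5 = 2.53, power 23%.
- Adjusted mean: residual variance 0.5 × 2.5/3 = 0.417; 27 × 0.0625/0.417 = 4.05, power 51%.
- Adjusted T1: 27 × 0.0625/0.75 = 2.25, power 32%.
- Joint test: λ = 4.05 on 3 df, power 35%.

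**Step 4: other cases, N = 108.**

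| Effect at T1/T2/T3 (SD) | r | Planned F | Adjusted mean | Adjusted T1 | Adjusted joint test |
|---|---|---|---|---|---|
| 0.25 sustained | 0.5 | 23% | 51% | 32% | 35% |
| 0.25 sustained | 0.8 | 54% | 77% | 57% | 60% |
| 0.40 sustained | 0.5 | 55% | 89% | 66% | 76% |
| 0.40 sustained | 0.7 | 79% | 96% | 82% | 88% |
| 0.5/0.35/0.25 | 0.5 | 59% | 83% | 84% | 76% |
| 0.4/0.2/0 | 0.5 | 51% | 36% | 66% | 57% |
| 0.4/0/0 | 0.5 | 55% | 19% | 66% | 57% |
| 0.4/0/0.4 | 0.5 | 69% | 57% | 66% | 76% |

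Simulation with 4,000 runs at r = 0.5 agrees for the planned F and the adjusted mean: 23.8% and 50.5% at 0.25 SD, 54.9% and 89.1% at 0.40 SD.

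**The case against.** **The gain is conditional, and can reverse.** This stands. The Background gives no time course, and the Procedure section places a booster session directly after the 3-month follow-up, so a dip at T2 with recovery at T3 is plausible. In the fading and dipping rows the T1-T3 mean loses to the planned test without any change of sign. T1 alone also falls slightly behind for 0.4/0/0.4.

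**A reader might infer that the change lifts power from about 54% to 87% or more.** Figures of that size need a sustained effect of about 0.4 SD and r of about 0.5. The article states neither, and its own effect is d = 0.25. They also apply to the T1-T3 mean, not to T1.

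**A reader might infer that the trial has less power than it states.** This check does not show that. The stated 106 is reproduced in Step 1. Read through that f, the effect is a sustained 0.125 × √18 = 0.53 SD, at which the planned four-occasion test has about 80.5% power with 106 participants.

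**A reader might infer that the planned test is invalid or unworkable.** It is not. Multiple imputation supplies complete rows, and rules exist for pooling tests with several degrees of freedom. In simulation the baseline-moderation test kept its type I error at about 0.05. Nor does the article establish a need for a random intercept for school or residential group.

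**The article is condensed and an unseen analysis plan may name a contrast.** This is fair as to the contrast and the interval, and the article does not say which F term decides. But the four-level ANOVA with the pre-test as a level, the conditional baseline adjustment and the moderator test in that same design are stated choices.

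**Conclusion.** The point holds as one of efficiency and coherence, not of validity. The stated model uses T0 as an outcome where it would serve better as a covariate, adjusts for it only on a significance test, and lets T0 mindset act as both moderator and outcome.

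For a sustained effect, the T0-adjusted T1-T3 mean was more powerful at every correlation tried (0.4 to 0.8). T1 alone gains much less, only about 3 points at r = 0.8 for d = 0.25. At d = 0.25 and 108 completers neither contrast reaches 80% in the range r = 0.5 to 0.8.

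The advantage of the mean rests on a sustained effect. What depends less on time course is the adjustment itself: the joint T0-adjusted test was about as powerful as, or more powerful than, the planned F in the patterns tried. All figures rest on compound symmetry and on assumed correlations and time courses.

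**What to change.** Analyse T1, T2 and T3 as outcomes, for example in a linear mixed model with unstructured covariance. Include arm, occasion, arm-by-occasion, the T0 score always as covariate, and the stratification factors gender, age and IQ. Drop the t-test rule for choosing covariates.

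Before the data are seen, name one primary contrast and report it with a 95% CI: the T1 difference, or the T1-T3 average if a sustained effect is expected. Treat the other time points as secondary. Test baseline-mindset moderation as arm × T0 score in this model.

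The cost is analysis wording only: no added participants, visits or measures. The price is that a single contrast commits to a time course. The T1-T3 mean gives up power if the effect fades to zero or dips before the booster (19% versus 55%, and 57% versus 69%, in the rows above). If the time course is genuinely uncertain, a joint test of the T0-adjusted arm differences keeps sensitivity to such patterns, at the cost of a direction and of some power against a sustained effect.
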